### Plans to give access to the full protocol, participant level-data and statistical code {31c}

The datasets generated and/or analyzed during the current study are not publicly available due to the European Union General Data Protection Regulation, but are available from the corresponding author on reasonable request.

### Composition of the data monitoring committee, its role and reporting structure {21a}

There will be no formal data monitoring committee independent from the sponsor or the trial steering committee. Patient safety will be protected by an independent third party who will bimonthly assess the harm of both treatment arms. This independent third party for safety has no conflict of interest with the sponsor of this trial. Stop criteria have been predefined by the trial steering committee (cfr. supra). If one of the stop criteria is reached, the independent third party for safety will discuss this with the central PI and the central Ethical Committee and a decision about prematurely stopping the trial will be formulated and communicated to all parties involved in the trial. A formal interim analysis for safety is planned when the 3-month follow-up data of the first 50 randomized patients are obtained.

### Adverse event reporting and harms {22}

Adverse events and postoperative complications will be assessed by the treating surgeon through thorough history taking, physical examination, or by any means necessary. If present, these adverse events and postoperative complications will be logged and categorized according to the Clavien-Dindo classification system [15, 16]. Treatment of adverse events and postoperative complications will take place according to the best standard of care of the participating center at hand.

### Frequency and plans for auditing trial conduct {23}

A yearly audit will be organized by the clinical trials unit of Ghent University Hospital’s “Health, Innovation and Research” department.

### Plans for communicating important protocol amendments to relevant parties (e.g., trial participants, ethical committees) {25}

All important protocol amendments will be communicated by e-mail to the central Ethical Committee and to all local PIs, who are in turn responsible to communicate this to their own local Ethical Committee.

## Dissemination plans {31a}

Trial results will be published in the format of an original article which will be submitted for peer review and publication in an A1 journal. Besides, an abstract of the trial’s results will be submitted for presentation at national and international scientific meetings. Trial results will be published irrespective of the direction or nature of the findings.

## Discussion

This study will provide evidence about whether vsAR yields non-inferior surgical results compared to tAR or not. This question has been subject to debate for over a decade, and yet, only retrospective research is available on this topic. To the best of our knowledge, this trial is the first randomized controlled trial to address the question at hand.

Beside the comparison of surgical outcome after both techniques, this trial will also investigate differences in change of functional outcome parameters between both techniques. This will further elucidate the true value of bulbar artery preservation and either refute or confirm the advocated theories about functional benefits.

Depending on the trial results, this phase II trial may be the basis for a larger phase III trial with more statistical power and a lower alpha value.

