To analyze change in erectile function and differences in change of erectile function between vsAR and tAR.❖ The International Index of Erectile Function (IIEF-5) questionnaire* will be administered to participants preoperatively and after 3, 12, and 24 months of follow-up.❖ The IIEF-5 questionnaire provides a summative score between 5 and 25 and should be interpreted as follows: 22–25 = no erectile dysfunction; 17–21 = mild erectile dysfunction; 12–16 = mild to moderate erectile dysfunction; 8–11 = moderate erectile dysfunction; 5–7 = severe erectile dysfunction.❖ De novo postoperative worsening of erectile function will be defined as a decrease of ≥ 5 points on the postoperative IIEF-5 questionnaire compared to the preoperative IIEF-5 questionnaire. This definition was chosen based on experts’ opinion, taking into account the lack of studies describing the ideal cut-off value to delineate “de novo erectile dysfunction” for this 5-item questionnaire [12].To analyze change in ejaculatory function and differences in change of ejaculatory function between vsAR and tAR.❖ The Male Sexual Health Questionnaire—Ejaculatory Dysfunction short form (MSHQ-EjD short form) questionnaire** will be administered to participants preoperatively and after 3, 12, and 24 months of follow-up.❖ The MSHQ-EjD short form questionnaire, consisting of 4 questions, provides a summative score between 1 and 15 (question 1–3) and a bother/satisfaction score between 0 and 5 (question 4).To analyze change in lower urinary tract symptoms (LUTS) and differences in change of LUTS between vsAR and tAR.❖ The International Consultation on Incontinence Questionnaire—Male Lower Urinary Tract Symptoms module (ICIQ-MLUTS module) questionnaire** will be administered to participants preoperatively and after 3, 12, and 24 months of follow-up.❖ The ICIQ-MLUTS module, consisting of 7 questions, provides a summative score between 0 (asymptomatic) and 24 (most symptomatic) (question 1–6) and a bother score between 0 (not bothersome) and 3 (very bothersome) (question 7).❖ Remark: The 7 questions of the ICIQ-MLUTS module questionnaire are only a subset of the entire ICIQ-MLUTS questionnaire. These 7 questions were chosen because of their relevance in a setting of urethral stricture disease and were validated in English, Dutch, and other languages (cfr. infra).❖ Peeling’s voiding picture** will be administered to participants preoperatively and after 3, 12, and 24 months of follow-up.❖ Peeling’s voiding picture provides a score between 1 and 4.To analyze change in urinary incontinence and differences in change of urinary incontinence between vsAR and tAR.❖ The International Consultation on Incontinence Questionnaire—Urinary Incontinence short form (ICIQ-UI short form) questionnaire will be administered to participants preoperatively and after 3, 12, and 24 months of follow-up.❖ The ICIQ-UI short form questionnaire, consisting of 3 scoring questions and 1 self-diagnostic question, provides a summative score between 0 (asymptomatic) and 21 (most symptomatic).To analyze change in quality of life and differences in change of quality of life between vsAR and tAR.❖ The EQ-5D-3L questionnaire** will be administered to participants preoperatively and after 3, 12, and 24 months of follow-up.❖ The EQ-5D-3L module, consisting of 5 questions, provides a 5-digit score in which every digit varies between 1, 2, and 3.❖ The EQ—Visual Analogue Scale (EQ-VAS)** will be administered to participants preoperatively and after 3, 12, and 24 months of follow-up.❖ The EQ-VAS provides a scale between 0 and 100.To analyze patient satisfaction and differences in patients’ satisfaction between vsAR and tAR.❖ Two specific questions regarding patient satisfaction will be asked at 3, 12, and 24 months.To analyze change in maximum flow rate (Qmax) and differences in Qmax between vsAR and tAR.❖ Uroflowmetry will be performed preoperatively and after 3, 12 and 24 months of follow-up.To analyze postoperative (< 90 days) complication rate and differences in postoperative (< 90 days) complication rate between vsAR and tAR.❖ Complications within the first 90 postoperative days will be categorized according to the Clavien-Dindo classification system [15, 16].

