#### Analysis of the secondary end-points

Postoperative changes in erectile function, ejaculatory function, LUTS, urinary incontinence, and quality of life will be analyzed by comparing the scores of the postoperative questionnaires with the scores of the preoperative questionnaires. For every participant, the 3-, 12-, and 24-month follow-up questionnaire scores will be compared to the respective preoperative questionnaire scores. Differences in scores will be logged for the 3-, 12-, and 24-month follow-up moment, and for each of these time-points, the median (interquartile range (IQR)) change in scores will be assessed for vsAR and tAR. Median (IQR) change in scores will be compared between vsAR and tAR using a two-sided Mann-Whitney *U* test at the 20% significance level.

As regards de novo postoperative worsening of erectile function, defined as a decrease of ≥ 5 points on the postoperative IIEF-5 questionnaire compared to the preoperative IIEF-5 questionnaire, a two-sided Fisher’s exact test at the 20% significance level will be used to compare vsAR and tAR at the 3-, 12-, and 24-month follow-up moment.

Postoperative patient satisfaction will be assessed at the 3-, 12-, and 24-month follow-up moment. For each time-point, the proportion of satisfied patients will be compared between vsAR and tAR using a two-sided Fisher’s exact test at the 20% significance level.

Postoperative change in Qmax will be compared between vsAR and tAR at the 3-, 12-, and 24-month follow-up moment using a two-sided Mann-Whitney *U* test at the 20% significance level.

Postoperative complications will be compared between vsAR and tAR using a two-sided Fisher-Freeman-Halton test at the 20% significance level.

Note that for all secondary end-points, participants will be censored at the moment they undergo a subsequent urethral treatment (dilation, urethrotomy, urethroplasty, or urinary diversion).

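### The Discussion promises to refute or confirm a functional benefit, but the plan rests on about 33 unadjusted 20% tests with no deciding outcome or visit

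*Protocol article*

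**What the plan says.** The Background and rationale explains the interest in vsAR chiefly by possible functional gains, erectile function among them. The Discussion then states what the trial will settle: "This will further elucidate the true value of bulbar artery preservation and either refute or confirm the advocated theories about functional benefits".

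The section Analysis of the secondary end-points sets out the tests:

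- Questionnaire scores: "Differences in scores will be logged for the 3-, 12-, and 24-month follow-up moment, and for each of these time-points" a median change is assessed per arm. Then: "Median (IQR) change in scores will be compared between vsAR and tAR using a two-sided Mann-Whitney *U* test at the 20% significance level".
- Erectile worsening (a fall of 5 points or more on the IIEF-5): "a two-sided Fisher’s exact test at the 20% significance level will be used to compare vsAR and tAR at the 3-, 12-, and 24-month follow-up".
- Flow rate: "Postoperative change in Qmax will be compared between vsAR and tAR at the 3-, 12-, and 24-month follow-up moment", again at 20%.
- Satisfaction is compared at each visit and complications once, both at 20%. The Outcomes section adds: "Two specific questions regarding patient satisfaction will be asked at 3, 12, and 24 months".

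The Sample size section bases both the number of patients and the case for a one-sided alpha of 0.10 on failure-free survival (FFS). It gives no functional effect size. The Discussion also says that the trial may lead to a larger phase III trial with more power and a lower alpha.

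**The concern.** To confirm a theory, a trial needs a result that would rarely arise by chance. To refute one, it needs enough precision to exclude a benefit that matters. The plan fixes neither for function. It has many tests at a lenient level, no stated test on which a functional conclusion rests, and no between-arm difference that would count as a benefit or rule one out. A change at 3 months, which may be transient, carries the same weight as a change at 24 months.

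The functional message is the reason to prefer vsAR once surgical non-inferiority is shown. Under the Discussion's wording, one isolated significant score could be reported as confirmation, or a non-significant erectile result as refutation.

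**Working it through.** **The plan's own figure.** For FFS, n per arm = (z₀.₉₀ + z₀.₈₀)² × [p_c(1 − p_c) + p_t(1 − p_t)] / (d − (p_c − p_t))². With 0.954, 0.953 and d = 0.10 this is 4.508 × (0.04388 + 0.04479) / 0.099² = 40.8, so 41, as stated. The protocol then enrols 50 per arm and expects 20% drop-out, leaving 50 × 0.8 = 40 evaluable. No functional outcome enters this calculation.

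**Number of tests** (from Outcomes and Analysis of the secondary end-points).

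| Measures | Visits | Tests |
|---|---|---|
| 9 scores: IIEF-5; MSHQ-EjD sum and bother; ICIQ-MLUTS sum and bother; voiding picture; ICIQ-UI; EQ-5D-3L; EQ-VAS | 3 | 27 |
| Qmax | 3 | 3 |
| Erectile worsening | 3 | 3 |
| **Functional subtotal** | | **33** |
| Satisfaction (one or two questions) | 3 | 3 or 6 |
| Complications | 1 | 1 |
| **All** | | **37 or 40** |

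Other readings run from 31 (no bother scores, one satisfaction test) to 55 (each EQ-5D digit tested, two satisfaction questions, three per-protocol tests).

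**Can a significant result confirm?** Suppose the arms do not differ.

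- Expected significant results at the nominal level: 33 × 0.20 = 6.6, of which 33 × 0.10 = 3.3 favour vsAR.
- If the tests were independent, the chance of at least one in either direction would be 1 − 0.8³³ = 0.999. They are not independent, so I simulated correlated normal test statistics. The correlations are assumptions: 0.3 to 0.5 between measures and 0.6 to 0.9 between visits.

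| Measures × visits | At least one, either direction | At least one favouring vsAR |
|---|---|---|
| 11 × 3 (functional) | 0.92 to 0.99 | 0.54 to 0.77 |
| 12 × 3 (satisfaction added) | 0.94 to 0.995 | 0.56 to 0.78 |

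The simulation gives every test its full 20% size. Fisher's exact test is conservative: at 40 per arm its real size is about 5%, 9% and 13% for common rates of 5%, 10% and 20%. The erectile-worsening tests therefore contribute less than the simulation assumes.

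**Can a non-significant result refute?** Take 40 per arm and a two-sided 20% test. The erectile-worsening rates are assumed, because the protocol gives none.

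| Erectile worsening, tAR vs vsAR | Exact Fisher power |
|---|---|
| 20% vs 10% | 38% |
| 15% vs 5% | 43% |
| 30% vs 15% | 54% |
| 20% vs 5% | 69% |
| 30% vs 10% | 78% |

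For 20% versus 10%, the 80% CI half-width is 1.2816 × √(0.2 × 0.8/40 + 0.1 × 0.9/40) = 0.101, about 10 points.

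For a continuous score (normal approximation), the difference detectable with 80% power is (1.2816 + 0.8416) × √(2/40) = 0.47 SD. Power is 35% at 0.2 SD and 52% at 0.3 SD. The 80% CI half-width is 1.2816 × √(2/40) = 0.29 SD.

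**The case against.** The strongest reply is that one Discussion sentence is not a decision rule. The only formal hypothesis concerns FFS, the secondary aims are worded as analysing change and differences in change, and the same Discussion foresees a phase III trial with a lower alpha. Unadjusted secondary tests at 20% are ordinary in phase II, and a hierarchy is often left to a statistical analysis plan. All of this stands. It makes the fault one of wording joined to design, and it means that neither the 20% level nor the absence of an adjustment method is an error in itself. But the sentence and the per-test 20% levels are fixed in this document, and together they claim something that the design does not deliver.

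Second, erectile function is already prominent. It is listed first among the secondary end-points, has a defined worsening threshold, has its own per-protocol analysis and is the only functional outcome in the interim stop criteria. That is true and narrows the point. Yet it is tested both as a score and as a binary outcome at three visits, and none of these six tests is named as deciding.

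Third, only results favouring vsAR could be taken as confirmation, and complications and satisfaction are not functional measures. Both corrections are accepted: the count that bears on the claim is about 33 and the relevant error rate is the directional one.

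**Conclusion.** The wording claims more than the functional analysis can support. A scattered significant result would not confirm a benefit, because one favouring vsAR arises by chance with probability of roughly 0.54 to 0.78. A non-significant result would not refute a moderate benefit, because power at 40 per arm is 38% for erectile worsening of 20% versus 10% and reaches 80% for a score only near 0.47 SD. These sizes rest on assumed correlations, assumed worsening rates and the protocol's own 20% drop-out. The lack of a deciding comparison does not depend on them.

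A reader might infer that the trial can do neither under any circumstances, or that a spurious vsAR benefit is almost certain. The documents do not support either. Large effects are detectable (78% power for 30% versus 10%), and the chance above 99% needs independent tests and counts differences in both directions. The primary FFS analysis is not affected.

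**What to change.** 1. In the Discussion, replace the promise to refute or confirm with a statement that the trial estimates functional differences and generates hypotheses. This agrees with the phase III remark in the same section. Add that a non-significant result does not exclude a benefit.
2. Name one lead functional comparison at one visit, reported with its CI, as the one on which a statement of functional benefit may rest. Change in IIEF-5 at 24 months, the horizon of the primary end-point, is one example; other choices are defensible.
3. Label the remaining 20% tests in Analysis of the secondary end-points as exploratory and unadjusted. They need not be dropped.

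The cost is wording only, with no new patients, visits or data. The downside is that fewer outcomes can support a claim. Timing matters: enrolment began in September 2018, outcome assessors and analysts are not blinded, and the safety interim compares 3-month erectile worsening with the trial coordinator taking part. The choice must be fixed and dated before comparative functional data are examined.

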## Trial status

The first patient was included on September 29, 2018. All trial participants are scheduled to be enrolled by January 2021. The outlined protocol is protocol version 1.2 (November 12, 2019).

## Abbreviations

AR: Anastomotic repair
CI: Confidence interval
FFS: Failure-free survival
ICUD: International Consultation on Urologic Diseases
ICIQ-MLUTS: International Consultation on Incontinence Questionnaire—Male Lower Urinary Tract Symptoms module
ICIQ-UI: International Consultation on Incontinence Questionnaire—Urinary Incontinence
ICH-GCP: International Council for Harmonization of Technical Requirements for Pharmaceuticals for Human Use—Good Clinical Practice
IIEF: International Index of Erectile Function
IQR: Interquartile range
ITT: Intention-to-treat
LUTS: Lower urinary tract symptoms
MSHQ-EjD: Male Sexual Health Questionnaire—Ejaculatory Dysfunction
PI: Principal investigator
PP: Per-protocol
Qmax: Maximum flow rate
RUG: Retrograde urethrography
SD: Standard deviation
tAR: Transecting anastomotic repair
VAS: Visual Analogue Scale
VCUG: Voiding cysto-urethrography
VeSpAR: Vessel-sparing anastomotic repair
vsAR: Vessel-sparing anastomotic repair
